### Sample size calculation

Assuming a baseline PTB rate of 16.2% [25], and expecting the intervention to reduce this to 4.7% [32], a sample size of 128 per group is required to detect this difference with 80% power at a 5% significance level. Accounting for a 20% attrition rate, the total sample size is set at 480 (160 per group).

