Although the relationship between oral health during pregnancy and birth outcomes has garnered increasing attention, effective oral care strategies for the prevention of PTB and LBW remain underexplored. Most interventional studies have found that basic periodontal treatment, which consists of scaling to remove plaque and calculus above the gingival margin and root planing to remove calculus below the gingival margin, is insufficient to prevent PTB and LBW [29, 30]. However, recent systematic reviews and meta-analyses suggest that combining scaling and root planing (SRP) with routine oral care using mouthwash containing chlorhexidine gluconate (CHG) may reduce the risk of PTB and LBW by approximately half (PTB: RR = 0.56; LBW: RR = 0.47) [31]. Another review found that the same combination significantly reduced the risk of PTB (OR = 0.29) and the composite outcome of PTB and/or LBW (OR = 0.18) [32]. The most recent meta-analysis further supported the effectiveness of combining SRP with any mouthwash, reporting a pooled RR of 0.44 for PTB and 0.33 for LBW [33]. Despite these promising results, there remains a lack of well-designed randomized controlled trials (RCTs) to confirm the effectiveness of this combined approach [31–33].

Given the urgent need to establish effective oral health management strategies for pregnant women, integrating oral health care into the MNCH CoC represents a promising and potentially scalable approach. This study therefore aims to (1) assess whether the association between periodontal disease and adverse birth outcomes observed in previous research is also evident in our study population, and (2) evaluate the effectiveness of an integrated intervention, combining SRP and CHG mouthwash use, delivered through MNCH CoC, in preventing PTB and LBW. This RCT will also examine the intervention’s impact on maternal periodontal status and oral health-related quality of life (OHRQoL). Demonstrating the effectiveness of this intervention could provide critical evidence for incorporating oral health into broader MNCH strategies. We believe this study offers a unique and timely contribution to improving MNCH outcomes through an oral health approach.

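### The 4.7% intervention preterm-birth rate appears to apply an odds ratio as a risk ratio; the cited odds ratio gives 5.3%, and 80% power at 128 per group is then not secure

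*Protocol article*

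**What the plan says.** The protocol article, under Sample size calculation, sets the two rates: "Assuming a baseline PTB rate of 16.2% [25], and expecting the intervention to reduce this to 4.7% [32". From these it derives 128 per group for 80% power at the 5% level, and 160 per group (480 in total) after 20% attrition. It names no formula or test, does not say whether the test is two-sided, and does not show how 4.7% was obtained.

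The Background section describes what the same reference [32] found: "Another review found that the same combination significantly reduced the risk of PTB (OR = 0.29". It also quotes two other pooled estimates for preterm birth. Reference [31] says the combination "may reduce the risk of PTB and LBW by approximately half (PTB: RR = 0.56; LBW: RR = 0.47". Reference [33], on scaling and root planing with any mouthwash, is described as "reporting a pooled RR of 0.44 for PTB".

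Under Statistical analyses, the effect of the intervention on birth outcomes is the comparison of group A with group B, in a regression model adjusted for covariates.

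**The concern.** One reference supports both the 4.7% and the 0.29, and 4.7% is what results when 16.2% is multiplied by 0.29. That product is valid for a risk ratio. The article reports 0.29 as an odds ratio, and at a control risk of 16.2% the two are not interchangeable: multiplying the risk by the odds ratio overstates the reduction.

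The sample size and the stated 80% power both rest on this rate. If it is too low, the planned difference is larger than the cited estimate supports, and the power for that estimate is lower than the article implies. A reader who later weighs the result for preterm birth against the stated 80% would be using the wrong yardstick.

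**Working it through.** **Inputs.** Control rate 16.2%, intervention rate 4.7%, 128 per group, 80% power, 5% level and 20% attrition (Sample size calculation). OR 0.29, RR 0.56 and RR 0.44 for preterm birth (Background). Assumed: a two-sided test, equal allocation, and 16.2% as the true rate in group B.

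**Step 1. Reproduce the plan's figure.** With d = p1 − p2 and p̄ the mean of the two rates, the uncorrected size is

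n = [1.96·√(2p̄(1−p̄)) + 0.8416·√(p1(1−p1) + p2(1−p2))]² / d².

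For 0.162 and 0.047, d = 0.115 and n = 109.9, so 110. The continuity-corrected size is

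n_c = (n/4)·[1 + √(1 + 4/(n·d))]² = 126.7, so 127.

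The article states 128. Other variants are further away: unpooled variance 108, arcsine 103, one-sided 87 (104 with correction). Fisher's exact test at 128 per group has 82.7% power for these rates, so it does not lead to 128 either. Attrition: 128/(1 − 0.20) = 160, as stated. The arithmetic is therefore right for the stated rates, to within one participant per group; what needs checking is the 4.7%.

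**Step 2. Where 4.7% comes from.** 0.162 × 0.29 = 0.04698, which rounds to 4.7%. The pair 16.2% and 4.7% implies

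- RR = 0.047/0.162 = 0.290
- OR = (0.047/0.953)/(0.162/0.838) = 0.255

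**Step 3. The odds ratio applied correctly.** Control odds 0.162/0.838 = 0.1933. Times 0.29 = 0.0561. Risk = 0.0561/1.0561 = 0.0531, so 5.3% (RR 0.33).

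**Step 4. Size with 5.3%.** Uncorrected 125.8, so 126 per group (158 after attrition). Continuity-corrected 143.6, so 144 per group (144/0.8 = 180 after attrition, against 160 planned).

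**Step 5. Power at 128 analysed per group.** Uncorrected: Φ{[d − 1.96·√(2p̄(1−p̄)/n)] / √([p1(1−p1) + p2(1−p2)]/n)}. Corrected: the same with d − 1/n in place of d.

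| Intervention rate | Basis | Corrected | Fisher exact | Uncorrected |
|---|---|---|---|---|
| 4.7% | as stated | 80.5% | 82.7% | 85.7% |
| 5.3% | OR 0.29 | 74.6% | 76.5% | 80.7% |
| 7.1% | RR 0.44 | 54.3% | 55.4% | 61.9% |
| 9.1% | RR 0.56 | 33.2% | 33.6% | 40.3% |

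Exact enumeration of the uncorrected chi-square test at 5.3% gives 82.6%, hence the range 81–83% for an uncorrected test.

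**Step 6. What a non-significant result could show.** With 16.2% in both arms and 128 each, the expected count is 20.7 events per arm. SE(log RR) = √(2 × 0.838/(128 × 0.162)) = 0.284, and the 95% interval for the RR is exp(±1.96 × 0.284) = 0.57 to 1.75.

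**The case against.** **The slip is small.** It moves the rate by 0.6 percentage points. The planned analysis is an adjusted regression, for which an uncorrected test is arguably the closer analogue, and there 128 per group still give 81–83% power. This stands, and it limits the weight of the point. It does not make 4.7% right, and the formula that nearly gives 128 yields 75%, so both figures need to be shown.

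**The derivation is inferred.** The article does not write out how it reached 4.7%, and the cited review is not at hand. A reader might infer that no cited source supports the figure, but the article alone cannot establish that. What it supports is narrower: no preterm-birth figure quoted in it corresponds to 4.7%, and the product with 0.29 matches to the rounding.

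**Choosing the larger effect is a design decision.** This also stands. A reader might take the powering on reference [32], rather than on RR 0.44 or 0.56, as part of the same arithmetic error. The documents do not support that. The halving is reported as a finding of earlier reviews, not as this trial's planned effect. Reference [32] concerns the same combination as the trial, while [33] covers any mouthwash. The low power under those ratios is worth disclosing, but it is not a mistake.

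**Low power does not make every null result uninformative.** A reader might infer that a non-significant result could never exclude a halving of risk. Step 6 shows otherwise: equal arms at 16.2% would give an interval whose lower limit, 0.57, lies above 0.5. Nor does the article say how a null result would be read.

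**Conclusion.** The intervention rate of 4.7% is wrong as written, unless another derivation from reference [32] can be shown. The quoted odds ratio gives 5.3%. On the continuity-corrected formula that nearly reproduces the plan's 128, the requirement becomes 144 per group, and 128 analysed give about 75% power. Fisher's exact test gives about 77%, and an uncorrected chi-square test 81–83%. The stated 80% is therefore not secure; whether it survives depends on a test the article does not name.

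This rests on a two-sided test, on 16.2% holding in group B, on exactly 20% attrition leaving 128 per group, and on an inferred sample size formula. The match between 4.7% and 16.2% × 0.29 is close to certain arithmetic; that this is how the figure was derived is a strong inference. The point should be fixed, but it leaves the design, the comparison of A with B and the analysis model untouched.

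**What to change.** In the sample size paragraph:

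1. Replace 4.7% by 5.3%, or show how 4.7% follows from reference [32] by another route.
2. Name the formula or test and state that it is two-sided.
3. Restate power at 128 analysed per group as about 75% with continuity correction and 81% without.
4. Add one sensitivity line, presented as such: power is about 54–62% for a risk ratio of 0.44 and 33–40% for 0.56.
5. Say that a non-significant result will be interpreted from the confidence interval. Do not state in advance that it cannot exclude a halving of risk.

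The cost is one paragraph and a less favourable power statement. No change in enrolment is asked for.

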### Interventions

All participants will receive oral health education at baseline. The intervention being tested in this trial is the combination of SRP and the daily use of CHG mouthwash during pregnancy.

#### Oral health education

Immediately after the baseline survey and dental checkup, all participants will receive oral health education through a 5-min video and a culturally tailored handbook in Bengali. Two versions of the handbook, developed by the study’s dental experts, will be distributed: one for group A and another for groups B and C. Topics include proper tooth brushing, fluoride toothpaste use, and tongue cleaning [34–36]. Each handbook includes a daily self-monitoring chart designed to promote habit formation and support the maintenance of consistent oral hygiene behaviors throughout pregnancy. Group A’s version also includes CHG mouthwash usage instructions.

To increase accessibility and engagement, the video is accessible via QR code for viewing on personal or hospital-provided electronic devices.

#### Basic periodontal treatment and mouthwash use

Participants in group A will receive SRP and CHG mouthwash immediately after baseline dental checkups. Group B will receive the same intervention after the endline checkup. SRP procedures will take 10 to 15 min per patient. CHG use involves rinsing after morning and evening toothbrushing. Participants will log their daily hygiene practices in the provided handbook. Group A will receive follow-up dental cleaning using a toothbrush during subsequent antenatal visits.

### Data collection and study outcomes

The primary outcome is PTB (< 37 weeks gestation). Secondary outcomes include LBW (< 2500 g), periodontal disease, and OHRQoL.

#### Surveys

Face-to-face interviews at baseline will collect data on socio-demographic characteristics, obstetric history, oral care behaviors, OHRQoL, and lifestyle. An endline survey, conducted post-delivery before hospital discharge, will obtain data on oral health care behaviors, OHRQoL, and lifestyle.

A structured questionnaire was developed in English, translated into Bengali, and then back-translated into English. The accuracy of the translation and reliability of the contents were reviewed by two native Bengali speakers with expertise in MNCH and dentistry. A pre-test was conducted to identify any biases or ambiguities and to assess whether the questions are culturally appropriate.

##### Socio-demographic data

Socio-demographic data, including age, marital status, education level, employment status, family structure, and birth history, will be collected. Information on household assets, such as the ownership of durable goods, housing characteristics, and access to utilities, will also be collected to estimate household socioeconomic status by principal component analysis [37].

##### Oral health

Data on oral hygiene practices, especially tools, timing, and frequency of oral care, and knowledge of the epidemiology and prevention of periodontal disease will be collected. OHRQoL will be assessed via the Oral Health Impacts Profile (OHIP-14) [38, 39]. The profile consists of 14 questions in seven domains: functional limitation, physical pain, psychological discomfort, physical disability, psychological disability, social disability, and handicap. Responses are recorded, using a five-point Likert scale to record the responses: never = 1, hardly ever = 2, occasionally = 3, fairly often = 4, and very often = 5. The total score will be dichotomized into high versus low impact, using a median split.

The presence of periodontal disease symptoms will be assessed, using ten questions from a self-report check list developed by the Japanese Academy of Clinical Periodontology [40]. The questions include items related to bad breath, sticky mouth, bleeding during toothbrushing, swollen/drooping/bleeding gums, and problems with the teeth. The presence or absence of any symptoms will be included in further analysis.

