#### Hypothesis

We hypothesize that integrating an intervention targeting periodontal disease—comprising SRP and CHG mouthwash use—into the MNCH CoC will reduce PTB and LBW, decrease the prevalence of periodontal disease, and improve OHRQoL.

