### Statistical analyses

The primary analysis will follow the intention-to-treat principle, whereby participants will be analyzed according to their assigned groups, regardless of adherence to CHG mouthwash use during pregnancy. Missing data will be handled using multiple imputation procedures available in the MI suite of Stata. To assess the robustness of the findings, sensitivity analyses will be conducted by comparing results from imputed and non-imputed datasets.

Data from the baseline and endline surveys, dental checkups, and antenatal records will be compared across groups to evaluate the effects of the intervention (SRP combined with CHG mouthwash use) on the primary (PTB) and secondary outcomes (LBW, periodontal disease, and OHRQoL). Initial analyses will include descriptive statistics for participants’ socio-demographic and other basic characteristics, followed by bivariate analyses to examine differences in baseline variables between groups A and B, and between groups B and C.

To estimate the causal effect of the intervention on birth outcomes, comparisons will be made between groups A and B. To investigate whether previously reported associations between periodontal disease and adverse birth outcomes hold in our population, groups B and C will be compared.

For multivariable analyses, two types of regression models will be employed. (1) Multiple regression models will be used to evaluate outcomes measured only at endline. (2) Mixed-effect regression models will be applied for outcomes assessed at both baseline and endline, accounting for potential intra-individual serial correlations in the residual.

Specifically, to assess the effectiveness of the intervention on birth outcomes (PTB and LBW), a multiple regression model will be used, with intervention status (group A or B) as the main predictor, adjusting for potential covariates (socio-demographic characteristics, lifestyle, pregnancy-related characteristics, and pregnancy outcomes). For oral health outcomes (periodontal disease and OHRQoL), mixed-effects regression models will be used, including intervention status (group A or B), time point (baseline or endline), and their interaction terms, while adjusting for potential covariates.

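### The OHIP-14 total, a secondary outcome, is cut to high/low at an unspecified sample median before the mixed model; analysing the full score would keep information at almost no cost.

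*Protocol article*

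**What the plan says.** Under *Oral health* (Protocol article, Methods), the 14 OHIP-14 items are coded "never = 1, hardly ever = 2, occasionally = 3, fairly often = 4, and very often = 5", so the total runs from 14 to 70. The same section then says: "The total score will be dichotomized into high versus low impact, using a median split". It names no pre-set cut-off, does not say which women or which visit supply the median, and mentions no analysis of the full score.

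The outcome has a formal role:

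- *Data collection and study outcomes*: "Secondary outcomes include LBW (< 2500 g), periodontal disease, and OHRQoL".
- *Hypothesis*: the intervention is expected to "decrease the prevalence of periodontal disease, and improve OHRQoL".
- *Surveys*: the score is taken at baseline, and the endline survey "will obtain data on oral health care behaviors, OHRQoL, and lifestyle".
- *Statistical analyses*: "For oral health outcomes (periodontal disease and OHRQoL), mixed-effects regression models will be used", with group, time point and their interaction for A versus B. A model of the same form is planned for B versus C.

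**The concern.** A score with up to 57 distinct values is reduced to two before a model that would accept it whole. A woman who improves by many points without crossing the cut counts as unchanged, while one who moves a single point across it counts as a full change.

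Two things are at stake. The first is precision on a secondary outcome that the hypothesis names. The second is interpretation. The cut is a sample quantity, so it is known only once data are in, and its meaning depends on whose median is taken. The text allows at least three readings (median per visit, pooled over visits, or baseline median applied to both), and they describe change over time differently.

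**Working it through.** **Inputs.** From *Sample size calculation*: preterm birth 16.2% versus 4.7%, 5% significance, 80% power, 128 evaluable per group, 160 after 20% attrition. From *Oral health*: range 14–70. Assumed: two-sided testing and, to begin with, a roughly normal score. The documents give no mean, SD or shape for OHIP-14, and no power for it.

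**The plan's own figure.** The two-proportion formula with continuity correction gives 127 per group, matching the stated 128 to within one; 128 / 0.80 = 160. So 128 is used below as the evaluable number per group.

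**Information kept, normal score.** The efficiency of a median split relative to the mean is 2/π = 0.637, a loss of 36%. Hence 128 × 0.637 ≈ 81 effective women per group.

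**Power at 128 per group.**

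- Full score: 80% power at d = (1.960 + 0.842) × √(2/128) = 2.802 × 0.125 = 0.350.
- Split at the same d: the proportions high are Φ(±0.175) = 0.569 and 0.431, a difference of 0.139. The standard error is √(0.5/128) = 0.0625 under the null and 0.0619 under the alternative. Power = Φ[(0.139 − 1.960 × 0.0625)/0.0619] = 60.5%.
- For 80% power the split needs 202 per group at that d, or d = 0.44 at 128 per group.

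| d | full score | split, formula | split, simulated |
|---|---|---|---|
| 0.30 | 67% | 48% | about 51% |
| 0.35 | 80% | 60.5% | about 64% |
| 0.40 | 89% | 72% | about 75% |

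The simulated column uses 20,000 trials, a pooled-median cut and an uncorrected two-proportion test. That test rejects about 6% of the time under the null because the statistic is discrete, which flatters the split. Hence the range of 60–64% at d = 0.35.

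**Dependence on shape.** A simulated 14-item, 1–5 score with a latent shift of 0.4, 128 per group and 2,000 trials gives:

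| shape | t-test, full score | rank test, full score | split | loss against t-test |
|---|---|---|---|---|
| symmetric | 87% | 85% | 70% | 36% |
| moderate right skew | 76% | 81% | 66% | 21% |
| strong floor (median at 14) | 55% | 67% | 58% | none |

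In the floor case, ties leave only about 39% of women in the high class.

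**Both visits split, baseline adjusted for.** With baseline–endline correlation r and φ = (2/π)·arcsin(r), the information kept is (2/π)(1 − r²)/(1 − φ²). For r = 0.5: φ = 0.333, and 0.637 × 0.75 / 0.889 = 0.537, a loss of 46%. For r = 0.3 and 0.7 the losses are 40% and 57%.

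**Whose median.** Suppose, for illustration, that A improves by 0.9 SD and B by 0.5 SD, with normal scores and equal groups. The share of women classed high moves as follows:

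- *Median per visit*: A 50% to Φ(−0.2) = 42%; B 50% to Φ(0.2) = 58%. B improved but appears to worsen. The A–B difference is still visible.
- *Pooled median* (cut at −0.35 SD): both start at Φ(0.35) = 64%; A ends at Φ(−0.55) = 29%, B at Φ(−0.15) = 44%. The cut moves with the endline data.
- *Baseline median*: both start at 50%; A ends at Φ(−0.9) = 18%, B at Φ(−0.5) = 31%. Overall improvement shows, and the cut does not depend on endline data.

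**The case against.** The best defence has four parts, and much of it stands.

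- **The size is not fixed.** The 36% loss rests on normality, and a quality-of-life score in young women may well be skewed or sit at its floor. This stands: the loss could be 21%, or nil against a t-test. But even with a strong floor the split has less power than a rank test on the full score (58% versus 67%), so no shape examined makes it the best use of the data.
- **The treatment contrast survives.** A reader might infer that a per-visit median makes the treatment effect disappear. It does not. It fixes the overall share classed high among the women who set the median, which damages the time effect and any statement of improvement; the group-by-time contrast between A and B remains estimable. If group C helps set the median, A and B together need not split evenly either.
- **A sensible reading exists.** Nothing in the text rules out a baseline median used at both visits, which removes the by-construction problem and the dependence on endline data. It does not restore the lost information.
- **The stakes are limited.** OHRQoL is one of several secondary outcomes, and no power is claimed for it.

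Two further inferences are not supported. The periodontal symptom checklist is also reduced ("The presence or absence of any symptoms will be included in further analysis"), but it is not listed as an outcome, may serve only as a covariate, and the documents do not say how many women report any symptom. Nor do the documents show that results could not be compared with other OHIP-14 studies: item responses are recorded on the full scale, so totals can still be reported.

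**Conclusion.** The concern holds as a matter of efficiency and clarity for a secondary outcome. The article itself fixes the split, and nothing elsewhere in it cancels that. Under a roughly normal score, the split costs about 36% of the information: at 128 per group and d = 0.35, power is about 60–64% instead of about 80%. That figure depends on an assumed distribution and should be quoted with its range: about 21% under moderate right skew, possibly none against a t-test at a strong floor, and about 40–57% if both visits are split and baseline is adjusted for. The unspecified median adds an ambiguity that matters for statements about change over time, less so for the A–B comparison. A reader should not conclude that the trial's main question is weakened: the preterm-birth analysis and the sample size are untouched. The change should be made because it is better and nearly free.

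**What to change.** In *Oral health* and *Statistical analyses*, state that:

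- the OHIP-14 total (14–70) is analysed as a continuous score in the mixed model already planned, or as the endline score adjusted for baseline, and reported as a mean difference with its confidence interval;
- a rank-based or ordinal analysis of the full score is the sensitivity analysis in case of skew or a floor (robust standard errors alone would repair inference but not efficiency);
- any high/low version is descriptive only, at a cut-off fixed before endline data are seen, for example the baseline median applied at both visits, with the women who set it named.

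The cost is wording in the analysis plan. The item responses are already collected, so no visit, procedure or recruitment target changes.
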